## Methods/design

This full clinical trial complies with the revised Helsinki declaration (cf. Fortaleza, Brazil, 2013), as well as Germany’s laws for data security (i.e., General Data Protection Regulation of the German Data Protection Act). Ethical approval of the study has been obtained from the ethics committee of the German Sport University Cologne (GSU, application number 104/2021). This approval covers all four study sites (Cologne, Bonn, Dusseldorf, and Bremen; addresses are included at the end of the protocol).

The study was prospectively registered in the German Clinical Trial Register (registration number: DRKS00025897).

### Study design

The study design is a multi-site randomised controlled longitudinal intervention study which includes four comprehensive assessments: T_0_, T_1_, T_2_, and T_3_ for all participants. All participants are randomly assigned to either the intervention group (INT) or the control group (CTR; see randomisation procedures). Figure 1 shows the SPIRIT-figure, including the schedule of enrolment, interventions, and assessments.

**Fig. 1 Fig1:**
[figure not shown]
SPIRIT-Figure: Schedule of enrolment, interventions, and assessments (CTR = control group; HBEP = home-based exercise programme; INT = intervention group; TSEP = technology-supported exercise programme; X = relevant for INT and CTR; +  = only relevant for INT)

For the intervention group, T_0_ is a baseline assessment; T_1_ an assessment after finishing the technology-supported part of the intervention; T_2_ an assessment after finishing the home-based exercise programme; and T_3_ a final follow-up assessment 12 months after T_2_. In total, the training period of the intervention group comprises 2*24 units (48 sessions in total) with a training frequency of two planned training sessions of 30 min each per week. The intervention period of the technology-supported exercise programme is individually dependent on the time progress of the completed 24 sessions. Given the defined training frequency of two training sessions per week, the technology-supported exercise programme has a minimum intervention period of 12 weeks. If individual training sessions are cancelled, the intervention period may be extended, however, it is limited to a maximum of 16 weeks. Identical to the intervention period of the technology-supported exercise programme, the period of the home-based programme is then determined individually for each participant. Participants in the control group receive all four measurements. Participants in the control group are not offered any actions; they are instructed to maintain their activities as usual. The time periods between the T_0_, T_1_ and T_2_ measurements are defined as 16 weeks for the control group. Both groups end at T_3_ with a final follow-up assessment 12 months after T_2_. Figure 2 shows the detailed timeline for study participants. Participants in the control group will have the opportunity to participate in an optimized training programme using the hunova robot after the end of the study.

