**Methods:**

The full clinical trial incorporates community-dwelling older adults at risk of falls with a minimum age of 65 years. Including a one-year follow-up measurement, all participants are tested four times. The training programme for the intervention group comprises 24-32 weeks in which training sessions are scheduled mostly twice a week; the first 24 training sessions use the hunova robot, these are followed by a home-based programme of 24 training sessions. Fall-related risk factors as secondary endpoints are measured using the hunova robot. For this purpose, the hunova robot measures the participants’ performance in several dimensions. The test outcomes are input for the calculation of an overall score which indicates the fall risk. The hunova-based measurements are accompanied by the timed-up-and-go test as a standard test within fall prevention studies.

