#### Fall diary

To assess the number of falls, participants are instructed to keep a diary throughout the complete study (i.e., between T_0_ and T_3_). In the context of this study, a fall is defined conform Lamb and colleagues [41] “a fall is an unexpected event in which the participant comes to rest on the ground, floor, or lower level”. In the fall diary, the participant indicates for each day whether one or more of following events [5] occurred; a ‘trip or slip’, a ‘fall without injuries’, or an ‘injurious fall’. In case of a fall, details of the fall are documented in a fall anamnesis questionnaire. After inclusion in the study, participants receive sheets for every month of their study participation. Sheets for completed months are collected every time the participants visit the study centres for assessments.

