#### Planned statistical evaluation of outcomes

An analysis of primary outcomes (i.e., number of falls and number of persons who have fallen) will be based on binomial regression analyses with demographic variables, physical activity, and health parameters as covariates. Analyses of secondary outcomes (SI and TUG) will be based on 2 × 4 ANOVA / ANCOVA with groups (INT/CTR) and time of assessment (T_0_, T_1_, T_2_ and T_3_) as factors, and will consider demographic variables, physical activity, and health parameters as co-variates. Significant main or interaction effects will be investigated further using Bonferroni post-hoc-tests. The significance level is set to *p* < 0.05.

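### Control participants are observed for a fixed 84 weeks and intervention completers for 76 to 84, and the article states no exposure time or common window for comparing falls and fallers

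*Protocol article*

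**What the plan says.** All of this is in the protocol article.

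- **Control arm (Study design):** "The time periods between the T_0_, T_1_ and T_2_ measurements are defined as 16 weeks for the control group".
- **Intervention arm (Study design):** "the technology-supported exercise programme has a minimum intervention period of 12 weeks". Cancelled sessions may lengthen it, but "it is limited to a maximum of 16 weeks". For the second block, "Identical to the intervention period of the technology-supported exercise programme, the period of the home-based programme is then determined individually for each participant". The Abstract (Methods) gives the total: "The training programme for the intervention group comprises 24-32 weeks".
- **End of observation (Study design):** "Both groups end at T_3_ with a final follow-up assessment 12 months after T_2".
- **Counting window (Fall diary):** "participants are instructed to keep a diary throughout the complete study (i.e., between T_0_ and T_3".
- **Analysis (Planned statistical evaluation of outcomes):** "primary outcomes (i.e., number of falls and number of persons who have fallen) will be based on binomial regression analyses". Demographic variables, physical activity and health parameters are the covariates listed.

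Expected key results places the primary outcomes in the training period plus the one-year follow-up. The closing paragraph of the Background instead calls the primary outcome fall incidence. No section mentions person-time, an offset or a counting window of equal length in the two arms.

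**The concern.** The control arm has been given the longest schedule that the intervention arm can have. An intervention participant's window can therefore be shorter than a control's but not longer. The schedule is set by arm, so randomisation does not balance it, and a larger sample does not remove it.

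A person observed for less time has less opportunity to fall. An unadjusted comparison of fall counts, or of the proportion who fell, then favours the intervention among completers even if training does nothing. The participants who finish their sessions fastest have the shortest windows. Both primary outcomes are affected, and in the hypothesised direction.

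**Working it through.** **1. Windows.** Twelve months is taken as 52 weeks.
- Control: 16 + 16 + 52 = 84 weeks.
- Intervention, minimum: 12 + 12 + 52 = 76 weeks.
- Intervention, maximum: 16 + 16 + 52 = 84 weeks.

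The 24 to 32 training weeks agree with the total in the Abstract.

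**2. Fall counts with no true effect.** At a constant and equal fall rate, the expected count ratio is (intervention weeks)/84.

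| Intervention window (weeks) | Count ratio | Apparent reduction |
|---|---|---|
| 76 | 0.905 | 9.5% |
| 78 | 0.929 | 7.1% |
| 80 | 0.952 | 4.8% |
| 82 | 0.976 | 2.4% |
| 84 | 1.000 | 0% |

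The trial is sized for a 23% reduction (A-priori estimation of sample size). The upper bound is 9.5/23 = 41% of that, and the midpoint 4.8/23 = 21%.

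**3. Fallers with no true effect.** With yearly risk p and a constant hazard h = −ln(1 − p), the proportion who fall within w weeks is 1 − exp(−h·w/52). The Background gives yearly risks of about 30% and, for higher-risk groups, 50%.
- p = 0.30: 40.6% at 76 weeks against 43.8% at 84, risk ratio 0.93. At 80 weeks it is 42.2%, risk ratio 0.96.
- p = 0.50: 63.7% at 76 weeks against 67.4% at 84, risk ratio 0.95. At 80 weeks it is 65.6%, risk ratio 0.97.

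**4. False-positive rate for fall counts.** The stated 181 participants give 90.5 per arm. The article gives no fall rate per person-year and no dispersion. I assume 0.69–1.5 falls per year (0.69 is the hazard at 50% yearly risk) and negative binomial dispersion k = 0.5–1. With μ0 and μ1 the expected falls per person in the control and intervention arms:
- SE² = (1/μ0 + 1/μ1 + 2k)/90.5
- shift = ln(84/w)/SE
- P(significant, favouring intervention) = Φ(shift − 1.96)

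Example: 0.69 falls per year, k = 1, w = 76. Then μ0 = 0.69 × 84/52 = 1.115 and μ1 = 0.69 × 76/52 = 1.008. SE = 0.207, shift = 0.100/0.207 = 0.48, and P = 7.0%.

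| Window (weeks) | P(false result favouring intervention) | Two-sided error |
|---|---|---|
| 76 | 7.0–10.3% | 7.7–10.7% |
| 80 | 4.2–5.3% | 5.6–6.4% |
| 84 | 2.5% | 5.0% |

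With k = 2 the two-sided error at 76 weeks is 6.8–7.2%.

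**5. After correction.** With an offset for log observed time, or with one window of equal length in both arms, the expected ratio under no effect is 1.000 and the two-sided error returns to 5%.

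**The case against.** **The article may simply be silent.** The analysis sentence names a model family and classes of covariate. It is not a full list of terms, and an offset is a detail that a condensed article may leave to an analysis plan. Binomial may be loose wording for negative binomial, with which an offset is usual, and fall incidence in the Background can be read as a rate. This stands in part. A reader might infer that the plan rules out an exposure adjustment, or has chosen a model that cannot handle counts, and the text supports neither. But the unequal windows are fixed in the article itself. The same method is named for the yes/no faller outcome, and an offset in the fall-count model would not correct that.

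**The size is a bound.** The 9.5% requires every intervention participant to complete all 48 sessions without delay. The Abstract says training is mostly twice a week, and the Study design section allows for cancellations. This stands: the range is 0 to 9.5%, and completion speed is not given.

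**The direction is not certain in the analysed sample.** The article assumes 30% dropout and, under Potential limitations and risk for bias, takes steps against dropout in the control arm particularly. Greater control dropout would shorten control exposure and push the other way. This also stands. A reader might infer that the intervention arm must look better by design, but the arithmetic shows that only for completers. Uncertain dropout is itself a reason to account for observed time.

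**Conclusion.** The point holds in this form: the protocol sets windows of unequal length by arm and does not say how either primary outcome allows for it. Among completers with no true effect, the fall-count ratio lies between 0.905 and 1.00, about 0.95 at the midpoint. The faller risk ratio is about 0.93–0.95 at 76 weeks.

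The window arithmetic is firm. The bias figures assume constant and equal hazards. The error rates rest further on the assumed fall rates and dispersion, 181 analysed, and a comparison without exposure adjustment. Dropout is not modelled and could alter the net size or sign. The effect is modest, but it bears on both primary outcomes and should be settled before the data are analysed.

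**What to change.** State the following in the analysis section:

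1. **Falls:** negative binomial regression with log(days of diary observed) as offset.
2. **Fallers:** matching exposure handling, by any one of time to first fall, complementary log-log regression with a log-time offset, or the same fixed window from T0 in both arms. Seventy-six weeks is a window that every completer reaches.
3. **If the fixed window is made primary:** report the full T0–T3 period with the offset as a sensitivity analysis.

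Truncation is one adequate choice among these and is not required if the other methods are used.

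The cost is analysis wording, because the diary is already kept by day. If the fixed window is primary, up to 8 weeks of diary data (84 − 76) per participant, in controls and slower intervention participants, leave the primary analysis.

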**Fig. 2 Fig2:**
[figure not shown]
Timeline: T_0_ is a baseline assessment; T_1_ is an assessment after finishing the first technology-supported part of the intervention; T_2_ is an assessment after finishing the home-based exercise programme; and T_3_ is a final follow-up assessment 12 months after T_2_. HBEP = home-based exercise programme; TSEP = technology-supported exercise programme

### Study centres

All assessments, the technology-supported exercise programme (TSEP), as well as two sessions in which participants receive instructions for the home-based exercise programme (HBEP) take place in participating study centres in Cologne, Bonn, Dusseldorf, and Bremen, respectively (addresses are included at the end of this protocol). From each centre, 2-4 sport or physio-therapists take part in the research study. Before the start of the intervention, all participating therapists are trained. This training includes several e-learning (online) modules that must be completed before on-site training begins. All training content of this examination is developed by the German Sport University in cooperation with Movendo Technology. The on-site sessions will be implemented by a researcher from the German Sport University together with a Movendo Technology specialist before the study starts to have a high standardisation and fulfil quality criteria for each training and exercising person.

### Participants and recruitment

The target group for the intervention consists of community dwelling older persons aged at least 65 years at an increased risk of falls. Recruitment of potential participants will be through Generali Health Solutions (GHS), who will address insured persons of “Generali Deutschland Krankenversicherung AG” (Generali Germany Health Insurance AG) and its subsidiary. Insured persons receive a personalised invitation letter in which they are asked to participate in the study. If they do not contact any of the study partners within the first two weeks after the initial invitation letter, they will receive a reminder letter. If an insufficient number of appointments at T_0_ is made, invited insured persons will receive phone calls. Inclusion criteria: aged at least 65 years; an increased fall risk (defined via a composite risk score (see further text)), ability to walk more than 6 m without assistance, residence within a maximal distance of 20 kms (as the crow flies) to the closest study centre. Exclusion criteria are: a) body height < 1.50 m; body weight > 150 kg (the hunova robot was designed and sized taking into consideration these anthropometric measures for the target population of the device. These choices impacted both the mechanical design and the sizing design of the device); level of care in Germany between 2 and 5 (In Germany, a distinction is made between five levels of care. For classification into a care level, the independence and abilities in six areas of life (mobility, mental and communicative abilities, behaviour and psychological problems, self-care, independent handling of illness- or therapy-related demands and burdens, as well as coping with them, organisation of everyday life and social contacts) are assessed using an instrument based on nursing expertise. Points are awarded for these six areas, which are weighted differently and lead to an overall score (up to a maximum of 100). This score is used for classification into one of the five care levels, which range from care level 1 (minor impairments of independence or abilities) to care level 5 (most severe impairments that are accompanied by special requirements for nursing care). The care level assigned determines the care insurance benefits that the person in need of care receives [39]); incapacity to be physically active over at least 30 min; medical surgery within the last 12 months at the spine, hip, legs, knees, feet (e.g. medical surgery after femoral neck fracture, medical surgery for the purpose of joint replacement or joint stiffening); acute cancer disease including chemotherapy, radiotherapy, biological or palliative therapy; dementia; Parkinson’s disease; multiple sclerosis; epilepsy; cardiovascular disease (e.g. cardiac arrhythmias, heart failure, poorly controlled hypertension, chest pain at rest or on exertion); b) depression, anxiety disorder, schizophrenia, that is not treated properly; consequences of a stroke that impair motor and cognitive functions and/or limitations within speaking substantially; serious respiratory disease (e.g. COPD - chronic obstructive pulmonary disease); Menière’s disease or another disease associated with vertigo; injury or condition that limits the sensitivity and/or motor function of the legs or feet (e.g. spinal stenosis, back pain that radiates to the legs, acute disc prolapse); problems reading information on a screen about 1 m away (e.g. on TV or on a computer screen) -with or without glasses; acute inflammation of the musculoskeletal system (e.g. arthritis, rheumatism in acute attack, ankylosing spondylitis (Bechterew’s disease) in acute attack, acute attack of gout); deep vein thrombosis or "open" leg (e.g. ulcer); the need to wear custom-made orthopaedic footwear (this does not mean shoe inserts) due to sensitivity disorders in the feet; bone fracture due to osteoporosis or noticeable physical changes (sharp decrease in height, increasing development of a hunchback) (list from the health questionnaire). Diseases from a) are “hard” exclusion criteria. If one (or more) of the other b) diseases is present, interested persons are advised to call the Generali health phone hotline to check if a study participation is still possible. Together with the invitation letter, all identified insured persons receive all study materials (detailed study information brochure, health questionnaire, informed consent) by mail. Upon signing the informed consent, they can participate in the study. They will then be tested and, if eligibility is confirmed, then randomly assigned to either INT or CTR. Randomisation procedures, contents of the intervention, as well as the assessments for determining eligibility and evaluating the intervention are described in next subsections.

### Randomisation procedures

An equal number of participants in the intervention and control group will be determined for each study centre. For this purpose, all eligible participants draw a lot with either INT or CTR after the baseline assessment. The number of lots for INT and CTR is equal and limited. Drawn lots are not returned to the lottery pot until all lots have been drawn. The examiners of the centres have no influence on the allocation to the groups, a change between groups is not possible.

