### Potential limitations and risk for bias

The recruitment of potential participants will be via Generali Health Solutions (GHS), who will address insured older persons of “Generali Deutschland Krankenversicherung AG” (Generali Germany Health Insurance AG) and its subsidiary who live in the close area of the participating study centres. They receive detailed study information. The recruitment process could potentially lead to a selective recruitment of those older adults who are intrinsically motivated to exercise and who are already physically active. The fact that our study included older adults with a higher fall risk (according to the Silver Index, > 40%), while still being able to do 30 min of physical activity, could potentially bias our results. This aspect should be kept in mind while interpreting the results of the study. All interested persons had to state that they were willing to be randomised in one of the two groups to minimise dropouts, particularly in the control group. Within the randomisation procedure, a random allocation of all available places for the study is made by drawing lots. The examiners of the centres have no influence on the allocation to the groups, a change between groups is not possible and group preferences are strictly not allowed. Since the therapists do both measurements and the supervision of the training sessions, blinding of assessors is not possible which yields an acceptable risk for bias. The measurements at T_0_, T_1_, T_2_ and T_3_ are standardised and performed in the same room in each study centre by the same assessor. Measurements should be scheduled at the same day of the week and at the same time of the day for the four measurements if possible. The control group does not receive any training treatment, but they obtain the opportunity to use an optimised training programme after the study is finished (including 1-year follow-up). The participants in the control group are instructed to maintain their usual physical activity during the study. Due to the potential bias and influence of different levels of physical activity, the amount is documented through the German PAQ-50 + during the study duration for both groups. With having a multi-centre study, a bias of regional differences should be minimised. Furthermore, health status of older adults can change over the study duration and influence participation, drop-out rate and results of the study. To gain insights here, the EQ-5D-5L is implemented.

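### Drawing lots without replacement from a finite, equal pot lets the therapists who run the entry test guess the next allocation better than chance, to an extent set by an unstated pot size

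*Protocol article*

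**What the plan says.** Under Randomisation procedures the article sets balance by centre: "An equal number of participants in the intervention and control group will be determined for each study centre". It describes the pot as follows: "The number of lots for INT and CTR is equal and limited", and "Drawn lots are not returned to the lottery pot until all lots have been drawn". On timing, "all eligible participants draw a lot with either INT or CTR after the baseline assessment". The stated safeguard is that "The examiners of the centres have no influence on the allocation to the groups, a change between groups is not possible".

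Other sections say who is involved. Study centres gives 2-4 sport or physiotherapists per centre. Participants and recruitment puts testing and confirmation of eligibility before random assignment. The Silver Index section makes a score above 40% an entry criterion. Potential limitations and risk for bias adds: "Since the therapists do both measurements and the supervision of the training sessions, blinding of assessors is not possible". That section accepts the lack of assessor blinding as a risk but does not mention that allocations might be predictable.

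**The concern.** A balanced pot emptied without replacement works like a permuted block run on site. After any imbalance in the draws, the under-drawn arm is more likely to come next. The people placed to keep the tally are the centre's therapists: those they train are INT, and those they test but do not train are CTR. They also conduct the T0 test that decides whether the next person enters.

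At stake is selection before allocation, which is a different bias from unblinded measurement after it. A therapist who expects a particular arm could, knowingly or not, let that affect how the test is conducted, when an appointment is booked, or how a doubtful eligibility question is settled. If the type of person entering then differs by arm, covariate adjustment removes only the part that was measured. The Silver Index is also a secondary outcome, so a distorted T0 value would enter that analysis directly.

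**Working it through.** **Inputs from the article**
- Equal INT and CTR lots, finite number, no return until the pot is empty (Randomisation procedures).
- One pot per centre: inferred from the per-centre balance rule.
- Order: test, confirm eligibility, draw (Participants and recruitment; Randomisation procedures).
- Therapists both measure and train (Potential limitations and risk for bias).
- Planned total 235 (A-priori estimation of sample size). 235/4 = 58.75, so about 60 per centre if the four centres are equal, which is an assumption.

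**Input not given:** pot size. I range it from 4 to 60; 60 is roughly one pot for a whole centre.

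The article states no figure for predictability, so there is none to reproduce.

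**Model.** A pot holds m INT and m CTR lots. The guesser names the arm drawn less often so far. This needs only the running tally, not the pot size, because the tally returns to zero whenever a pot empties.
- Expected correct guesses per pot = m + ½(4^m / C(2m, m) − 1).
- Expected lots at the end of a pot that are already determined = 2m/(m + 1). To use this, the guesser must also know the pot size.

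**Pot of 10 (m = 5).** 4^5/C(10,5) = 1024/252 = 4.063. Correct guesses = 5 + ½ × 3.063 = 6.53, or 65%. Determined lots = 10/6 = 1.67, or 17%.

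**Pot of 60 (m = 30).** 4^30/C(60,30) ≈ 9.75. Correct guesses = 30 + ½ × 8.75 ≈ 34.37, or 57%. Determined lots = 60/31 = 1.94, or 3%.

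| Pot size (assumed) | Correct guesses | Determined lots per pot | Share determined | In the trial, 4 × 60 participants |
|---|---|---|---|---|
| 4 | 71% | 1.33 | 33% | 60 pots × 1.33 ≈ 80 |
| 10 | 65% | 1.67 | 17% | 24 × 1.67 ≈ 40 |
| 20 | 62% | 1.82 | 9% | 12 × 1.82 ≈ 22 |
| 30 | 60% | 1.88 | 6% | 8 × 1.88 ≈ 15 |
| 60 | 57% | 1.94 | 3% | 4 × 1.94 ≈ 8 |

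**Check on the remedy.** The same formula applies to ordinary small blocks. A block of 4 gives 2.83/4 = 71% and a block of 6 gives 4.10/6 = 68%. An equal mix gives (2.83 + 4.10)/10 = 69%. Varying the size hides which lots are determined, but the tally still works, and 69% is worse than any pot of 10 or more in the table.

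**Cost of dropping forced balance.** With simple 1:1 randomisation of n people, the expected efficiency relative to an exact split is 1 − 1/n. For n = 60 in a centre that is 98.3%, a loss of about 1.7%.

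**The case against.** The strongest reply has four parts.

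1. **Knowledge of the pot.** A reader might infer that therapists know what the pot contains and foresee its last lots. The article says only that the lots are equal in number and limited. It gives no size and does not say whether staff are told it, and a condensed article may leave that to the full protocol. This stands: certainty is conditional on knowing or inferring the size, for instance after a first pot has emptied and been refilled. Guessing better than chance is not conditional on it.

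2. **The safeguard sentence.** A reader might infer that the statement "The examiners of the centres have no influence on the allocation to the groups" is false. It is not. Participants draw their own lot and cannot change group, and the sentence is consistent with that. It covers tampering and switching. It does not address foreknowledge, or influence on who is enrolled.

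3. **Narrow routes.** Invitations and reminders go through the insurer's health company, health criteria come from a mailed questionnaire, doubtful conditions go to the insurer's hotline, and the Silver Index is calculated from device parameters under standardised measurement. This narrows the opportunity but does not close it. The index also uses the reported falls of the past 12 months, walking, sit-to-stand and limits-of-stability tests. In my judgement some of these respond to instruction and encouragement, but the article does not say so, and how far a score could be moved across 40% is unknown.

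4. **Size.** The 17% figure belongs to an assumed pot of 10. A centre-sized pot fits the text equally well and gives 3%. This stands, so only the range should be quoted.

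**Conclusion.** The allocation procedure as written is partly predictable at any finite pot size, and the people best placed to predict it also conduct the test that decides entry. Correct guesses run from about 65% (pots of 10) to about 57% (one pot of about 60 per centre), against 50% for unpredictable allocation. Allocations that are certain once the pot size is known run from about 17% to about 3%. Pots smaller than 10 would be worse.

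These figures rest on an assumed pot size, one pot per centre, and therapists who learn the earlier allocations at their centre. Trial-wide counts also assume four centres of about 60. The documents show opportunity only: they do not show that selection took place, and no bias in the treatment effect can be estimated from them. The change is worth making because it is cheap and the Data Availability statement says recruitment was still under way.

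**What to change.** For the remaining participants, replace the on-site pot with a computer-generated list, stratified by centre and held at the coordinating university. Release it for one participant at a time, by telephone or web, only after the T0 Silver Index result and the eligibility decision have been irrevocably recorded. Within centre, use unrestricted randomisation, or large blocks of varying size that are not disclosed to the centres. Do not use small blocks such as 4 or 6, which would be more guessable than a large pot.

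Report the pot sizes used so far, and compare baseline Silver Index by arm before and after the change. If recruitment has closed, the pot sizes and order of draws can still be reported, with baseline Silver Index by arm and position in the pot.

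The cost is a small amendment and one central list, with no extra centre staff. Unrestricted randomisation gives up exact equality of the arms within each centre, for an expected precision loss of about 1.7% in a centre of 60; large blocks keep the split closer. The method changes during recruitment, and this must be documented.
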